## Abstract

**Background:**

Increasingly, women elect breast reconstruction after mastectomy. However, their expectations of surgery are often not met, and dissatisfaction with outcome and ongoing psychosocial concerns and distress are common. We developed a patient-centered intervention, PEGASUS:(Patients’ Expectations and Goals: Assisting Shared Understanding of Surgery) which supports shared decision making by helping women clarify their own, individual goals about reconstruction so that they can discuss these with their surgeon. Our acceptability/feasibility work has shown it is well received by patients and health professionals alike. We now need to establish whether PEGASUS improves patients’ experiences of breast reconstruction decision making and outcomes. The purpose of this study is, therefore, to examine the effectiveness of PEGASUS, an intervention designed to support shared decision making about breast reconstruction.

**Methods:**

A multi-centered sequential study will compare the impact of PEGASUS with usual care, in terms of patient reported outcomes (self-reported satisfaction with the outcome of surgery, involvement in decision making and in the consultation) and health economics. Initially we will collect data from our comparison (usual care) group (90 women) who will complete standardized measures (Breast-Q, EQ5D -5 L and ICECAP- A) at the time of decision making, 3, 6 and 12 months after surgery. Health professionals will then be trained to use PEGASUS, which will be delivered to the intervention group (another 90 women completing the same measures at the time of decision making, and 3, 6 and 12 months after surgery). Health professionals and a purposefully selected sample of participants will be interviewed about whether their expectations of reconstruction were met, and their experiences of PEGASUS (if appropriate).

**Discussion:**

PEGASUS may have the potential to provide health professionals with an easily accessible tool aiming to support shared decision making and improve patients’ satisfaction with breast reconstruction. Results of this study will be available at the end of 2019.

**Trial registration:**

ISRCTN 18000391 (DOI 10.1186/ISRCTN18000391) 27/01/2016.

**Electronic supplementary material:**

The online version of this article (10.1186/s12911-017-0543-0) contains supplementary material, which is available to authorized users.

## Background

Mastectomy can have a considerable, long-term psychosocial impact for women worldwide. In England alone, more than 15,000 women undergo mastectomy each year and over 5000 elect breast reconstruction (BR) to surgically recreate a breast shape [1]. Options regarding BR timing and type are numerous, requiring women to make complex decisions amidst the emotional upheaval associated with cancer. Although BR aims to improve quality of life and appearance concerns, a national audit [1] reported worrying levels of dissatisfaction with surgical outcome, supporting previous reports of ongoing pain [2] and scarring [3]. BR is not a panacea for the distress of mastectomy [4] - almost half patients report some regret [5].

Women seeking BR anticipate it will restore a sense of ‘normality’, but their expectations of outcomes are often unclear [6, 7]. The decision is ‘preference-sensitive’ [8] because the ‘right choice’ depends on individuals’ personal preferences rather than generic treatment factors. Clarifying each patient’s preferences and values is imperative, central to shared decision making (SDM) [9] and key to patient-centred care [10]. However, treatment decision making often triggers breakdowns in communication between patients and health professionals (HPs) [11]. Patients and health professionals differ when rating the importance of facts and goals guiding decisions about reconstruction [8]. Whilst women make choices by drawing comparisons with their pre-cancer appearance, health professionals draw on their clinical experience of a wider range of post-surgical outcomes including appearance, pain, impact on physical activities, body image and wellbeing.

Women dissatisfied with the outcome of BR may seek further, corrective surgery (with implications for healthcare resources and distress for patients), and may maintain avoidance behaviours (e.g. intimacy, clothing choices) that BR was intended to reduce [6]. We surmise that if women have realistic expectations, then patient dissatisfaction, well-being and requests for additional surgery would improve. Although HPs need to ask women about their priorities and concerns [8], promote realistic expectations [12, 13], and support them making high quality decisions by empowering them through SDM [14], there are no interventions to help them elicit patients’ values, expectations and preferences. Instead, support typically focuses on information provision (e.g. websites, leaflets). However, increasing the amount of information available does not address erroneous expectations since it reinforces patients as passive recipients rather than actively engaged in setting clear, patient-centred goals (an approach associated with positive experiences and outcomes [15]. SDM has been heralded as a means of improving patient reported outcomes and satisfaction with cancer care [16] (particularly concerning preference sensitive decisions [17]) but implementation is difficult and slow [18]. Some decision aids for mastectomy patients are available [19, 20] but these are not BR-specific or focused around a face-to-face discussion centred on patients’ individual needs and the practicalities and possibilities of surgery. Nor do they explicitly help HPs and patients with the challenge of implementing SDM in this difficult and emotive situation. Clinicians report concerns that online interventions such as BRESDEX.com cannot be tailored to patients’ individual needs, and could replace nurses’ roles and induce patient anxiety if not provided under clinical supervision [20]. Recently, attention has shifted to decision coaching to facilitate patients’ preparation for SDM about preference sensitive decisions [21].

We developed an intervention to facilitate SDM by specifically helping patients and HPs clarify each woman’s motivations for BR (PEGASUS: Patients’ Expectations and Goals: Assisting Shared Understanding of Surgery) which is designed to elicit each patient’s own expectations of what she wants BR to achieve, facilitate setting patient centred goals (what she considers a successful outcome), and aid discussion of both physical and psychosocial expectations, goals and outcomes with their surgical team. PEGASUS is delivered to women previously informed about their reconstructive options, since physique and health status may render some procedures inappropriate. Unlike a purely paper-based intervention [19], PEGASUS involves meeting a decision facilitator (a specialist nurse/psychologist trained in its use who is referred to as the PEGASUS Coach) during which the patient is helped to identify her individual BR goals, what would indicate a successful outcome and the importance of each goal. She takes the completed PEGASUS sheet into the surgical consultation where it is used to inform shared goals and promote concordance between the patient and surgeon, so they approach surgical outcomes as a shared endeavour [22].

Interventions encouraging patients to prepare for and actively engage in consultations effectively improve satisfaction and health outcomes [23, 24]. PEGASUS facilitates the disclosure and discussion of expectations, enabling the surgeon to decide the extent to which they are realistic and, if necessary, take appropriate steps to address unrealistic expectations (e.g. explain the likely outcomes further, show more photographs). PEGASUS is a novel, well-accepted intervention that helps women express what they want and assist health professionals ‘diagnose’ their patients’ preferences – failure to do this is common and warrants interventions to “transform the role of patients in the NHS from passive users into active and engaged partners in care” ([25] pviii). Our work follows recommendations for developing and evaluating complex interventions [26]. Feasibility and acceptability testing is complete (conducted under NRES reference 11/NW/0788) and showed that PEGASUS is acceptable to both patients and health professionals alike [27]. We now need to establish whether using PEGASUS offers benefits over usual care – this is the aim of the current study.

## Method

### The main research question

Is a patient-centred, goal-focussed intervention (PEGASUS) that was developed to support shared decision making (SDM) for women contemplating breast reconstruction (BR) effective in terms of patient reported outcomes and costs?

### Aims of the study

To assess the efficacy of an intervention designed to:◦ elicit patients’ expectations of what reconstructive breast surgery will achieve◦ facilitate setting of patient-centred goals◦ facilitate discussion of these expectations and goals with the patient’s surgical team.
To explore whether the PEGASUS intervention improves patient reported outcomes (Breast Q) and reduces decisional conflict amongst women offered the option of breast reconstruction.To explore the economic costs of delivering the PEGASUS intervention compared with the costs of treatment as usual.To explore patients’ and health professionals’ experiences of using the PEGASUS intervention and its implementation within breast reconstruction services.

The research will be overseen and informed by the expertise of an advisory group consisting of patient representatives, a surgeon, clinical psychologist, specialist nurse, breast cancer charity representative and members of the research team.

### Design

A mixed methods (qualitative and quantitative methods), multi-centred, non-randomised between subjects, before-and-after design comparing usual care (control) with the intervention (PEGASUS). Randomised Controlled Trials (RCTs) are not necessarily suited for psychosocial research [28]. In this study it is inappropriate to randomize participants since contamination effects between conditions are likely if surgeons must focus some consultations around the patient goals offered by PEGASUS, but revert to usual care in others. In this non-randomised design, the control group comprises consenting patients receiving usual care. On completion of the control group recruitment, the health professionals receive PEGASUS training, prior to intervention group recruitment. Semi-structured interviews will be conducted with a selection of participants and health professionals involved in the PEGASUS intervention condition. Intervention consultations will be recorded (with permission) and assessed against a study-specific checklist to check the fidelity of the intervention.

### Trial design characteristics

The characteristics of the PEGASUS trial were assessed using PRECIS-2 [29]. PRECIS-2 is a tool specifically designed to assess trial design on a continuum of pragmatic-explanatory across nine criteria: eligibility, recruitment, setting, organisation, flexibility delivery, flexibility adherence, follow-up, primary outcome and primary analysis. Pragmatic trials aim to explore whether an intervention works in real-life settings whereas exploratory trials aim to explore whether an intervention works under ideal conditions [29, 30]. Figure 1 illustrates the trial design based on the nine criteria. Eligibility, recruitment, setting, follow-up and primary analysis follow a pragmatic approach, whereas organisation, flexibility delivery, flexibility adherence and primary analysis fall along the pragmatic-explanatory continuum.

**Fig. 1 Fig1:**
[figure not shown]
PRECIS-2

### Sites

Data collection will take place at hospital sites (Bristol, Bath, Truro, Winchester, and Cardiff) with comprehensive breast reconstruction services. The researcher will maintain weekly contact with each site, where clinic staff will identify eligible participants, provide study information and give the researcher the details of those who consent to participate.

### Sample size

One hundred eighty women over the age of 18 who have been diagnosed with breast cancer or DCIS (Ductal Carcinoma in Situ) or are seeking risk reducing surgery due to a strong family history of breast cancer, and who are considering breast reconstruction following mastectomy. We will record how many women are eligible for the study, how many participate and record reasons for refusal, where possible.

### Power calculations

The primary outcome measure is the Breast-Q (breast reconstruction) [31] with psychosocial wellbeing, sexual well-being, physical well-being and 5 satisfaction subscales applicable pre- and post-op and an expectations subscale applicable pre-operatively only. Sample size has been determined to ensure the simple comparison between the two groups 3–month post-operatively has at least 90% power (beta <= .20) using contemporary levels of significance (alpha = .05) in a two-sided test as this will ensure similar power requirements will be met for within group comparisons and for the anticipated interaction effect in the two-way ANOVA. An a priori power analysis based on a two-sided application of the independent samples t-test with an assumed lower estimate of a medium effect size (Cohen’s d = 0.5) indicates that at least 90% power would be achieved with a sample size of *n* = 90 per group. This stated power equates to at least 75% of women doing better in PEGASUS than they would have done with treatment as usual.

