### Analysis

The analyses will be described in detail in a full Statistical Analysis Plan but, in brief, the design permits a robust statistical analysis using a linear mixed model with random intercepts for longitudinal data, a one-way ANCOVA with baseline pre-op measure as a covariate, and t-tests for prior reasoned group comparisons. An adjusted ANCOVA will be used to account for the between-subjects non-equivalent groups design and this will prevent an overestimation of treatment effect due to measurement error. Primary analyses will be performed under multiple imputation using Multiply Imputed Chained Equations (MICE) and repeated on a complete basis. Data validity checks and missing values analysis will be undertaken prior to descriptive and inferential analysis. PEGASUS is intended for use with any surgical group and we will compare delayed with immediate reconstruction patients for any systematic differences in outcome.

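### The power paragraph pairs 90% power with a beta of .20, leaves no margin for missing 3-month scores, and promises interaction power that depends on an unstated correlation

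*Protocol article*

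**What the plan says.** The Power calculations section of the protocol article sizes the trial on the Breast-Q compared between groups 3 months after surgery. The target is "at least 90% power (beta <= .20) using contemporary levels of significance (alpha = .05) in a two-sided test". The method is a "two-sided application of the independent samples t-test" at Cohen's d = 0.5, and the section concludes that 90 per group achieves at least 90%. It adds that "this will ensure similar power requirements will be met for within group comparisons and for the anticipated interaction effect in the two-way ANOVA".

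The Sample size section gives the total as "One hundred eighty women over the age of 18" who are considering reconstruction. The abstract describes a usual-care group of 90 and then "another 90 women completing the same measures at the time of decision making" and at 3, 6 and 12 months after surgery. The planned total is therefore exactly 2 × 90.

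The Analysis section plans a random-intercept linear mixed model, "a one-way ANCOVA with baseline pre-op measure as a covariate", and t-tests, with the primary analyses under multiple imputation. The article gives no loss rate, no baseline to follow-up correlation and no effect size for the interaction.

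**The concern.** Power is one minus beta, so the two figures in the target describe different designs, and a reader cannot tell from that phrase which one was adopted.

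The 90 per group that the t-test calculation uses is also the whole planned sample. The stated power therefore assumes that nearly every woman has a 3-month score, while the plan itself provides for missing data.

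A between-group t-test at a single time point says nothing definite about a group-by-time interaction, because the precision of a change depends on how strongly baseline and follow-up scores correlate.

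At stake is how the result is read. If the trial is null, the 90% figure will be used to judge how strongly that counts against the intervention. It should then be the power for the analysis and the number of women actually available.

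**Working it through.** **Inputs from the article.** Two-sided alpha .05, d = 0.5 (SD = 1), 90 per group, independent-samples t-test at 3 months (Power calculations); total of 180 (Sample size).

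**Inputs assumed, because the article gives none.** Loss of 3-month scores of 10% to 30%, equal in both groups; baseline to 3-month correlation ρ from 0 to 0.5; no group difference at baseline; equal SD at both times.

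**1. Reproducing the stated power.** With n per group, the t statistic is noncentral t with 2n − 2 degrees of freedom and noncentrality d × √(n/2). For n = 90 this is 0.5 × √45 = 3.354 on 178 degrees of freedom, against a critical value of 1.973. Power is 91.6%, so beta = 1 − 0.916 = 0.084. The statement that 90 per group gives at least 90% is correct with full data.

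**2. Which target the sample size fits.** The same formula needs 86 per group for 90% (90.3%) and 64 per group for 80% (80.1%). The chosen 90 fits the 90% target, that is, beta ≤ .10.

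**3. Missing 3-month scores, unadjusted t-test.**

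| With a score, per group | Loss | Power |
|---|---|---|
| 90 | none | 91.6% |
| 86 | 4 women | 90.3% |
| 85 | 5 women | 89.99% |
| 81 | 10% | 88.5% |
| 72 | 20% | 84.6% |
| 63 | 30% | 79.5% |

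**4. Interaction.** For baseline against 3 months, the group-by-time interaction is a t-test on change scores. The SD of a change is √(2(1 − ρ)), so the effect size is 0.5/√(2(1 − ρ)). At 90 per group:

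| ρ | Effect size | Power |
|---|---|---|
| 0 | 0.354 | 65.5% |
| 0.2 | 0.395 | 75.1% |
| 0.3 | 0.423 | 80.5% |
| 0.4 | 0.456 | 86.1% |
| 0.5 | 0.500 | 91.6% |

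In steps of 0.005, power first reaches 90% at ρ = 0.475. At ρ = 0.5 the SD of the change equals that of a single score, so the power matches the t-test exactly.

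An overall four-time-point interaction F-test, with d = 0.5 at all three follow-ups and equal correlations between times, shows the same dependence: 67.7% at ρ = 0, 83.9% at 0.3 and 94.5% at 0.5.

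**5. Within-group comparisons.** If the change within a group is itself 0.5 SD, a paired test on 90 women has 91.3% power at ρ = 0 and 97.8% at ρ = 0.3. This part of the claim is reasonable on that assumption.

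**6. The baseline-adjusted ANCOVA already planned.** Adjustment reduces the residual SD to √(1 − ρ²), so the effect size is 0.5/√(1 − ρ²). At 72 per group, ρ = 0.3 gives 0.524 and 87.8% power; ρ = 0.5 gives 0.577 and 93.1%. At 81 per group the powers are 91.2% and 95.5%.

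**The case against.** The sample-size calculation is right. It reproduces at 91.6%, the section states the 90% target twice, and a power of 90% does satisfy beta ≤ .20 as an inequality. The beta is a labelling slip with no effect on the number recruited. That stands, but the label is still wrong as the definition of the target.

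A reader might infer that the trial is underpowered. The documents do not support this:

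- Falling below the threshold at 85 per group means 89.99%, which is trivial in itself.
- The 90% line at 86 per group applies only to the unadjusted complete-case t-test. The planned ANCOVA can hold about 90% under moderate loss.
- The abstract can be read as 90 women per group completing follow-up, although the total of 180 shows no margin.
- Women who decline reconstruction are not necessarily lost: the Measures section provides a mastectomy version of the Breast-Q.
- Multiple imputation and the mixed model can recover part of a missing 3-month score from the other time points.

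A reader might also conclude that the power does not carry over to the interaction. That is too strong: from a correlation of about 0.475 it does, and nothing in the article indicates a low correlation. What fails is the unconditional guarantee.

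Nor is it a fault that the Analysis section does not name a two-way ANOVA. That section is a summary, and its mixed model for longitudinal data is the usual counterpart.

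**Conclusion.** The point holds as a misstatement of the design's power properties, not as a failure of the design. Three things are wrong as written.

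- The beta contradicts the 90% target that the sample size was built to meet.
- The stated power applies to a sample with almost no missing 3-month scores. For the unadjusted t-test it would be about 85% at 20% loss.
- The promise of similar power for the interaction does not follow from the calculation. Over correlations from 0 to 0.4, change-score power is between 65.5% and 86.1%.

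The first point needs no assumption. The size of the second rests on assumed loss rates, and that of the third on assumed correlations and no baseline difference. The ANCOVA figures share those assumptions. In this non-randomised comparison, a baseline imbalance or the planned adjustment for measurement error would lower them somewhat.

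**What to change.** Revise the power paragraph, and carry the same figures into the statistical analysis plan:

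1. Change beta to ≤ .10.
2. State the number per group expected to have a 3-month score, with the loss rate assumed, and give the power at that number. Preferably do so for the baseline-adjusted ANCOVA: at 72 per group this is about 88% at a correlation of 0.3 and 93% at 0.5, against 84.6% for the t-test.
3. Delete the sentence on within-group and interaction power, or give it with the assumed correlation and effect sizes.

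This costs one paragraph of rewording. Recruitment, data collection and the planned analyses do not change. The downside is a stated power that looks somewhat less favourable and openly depends on its assumptions.

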### Exclusion criteria

Women who, for any reason, are unsuitable for breast reconstruction or unable to participate in an intervention and study conducted in English will not be eligible to participate. We acknowledge this limitation, but do not currently have the resources needed to offer PEGASUS in other languages. If this study is successful we will explore its use with women with limited English proficiency (LEP) in future research.

### Intervention training

Specialist nurses, psychologists and surgeons at each site will be trained to use PEGASUS by AC (the clinical psychologist in the study team) and the study researcher (NP). Face-to-face training will be supplemented by a manual and video footage demonstrating its use, accessible throughout the study. Feedback on this training (elicited in the health professional interviews and questionnaires at the training sessions) will identify whether edits are needed prior to making training resources available through the PEGASUS website (www.pegasusdecisionmaking.com) in any subsequent roll-out of the intervention.

### Procedure (see Additional file 1)

Potential participants will be identified by clinic staff at each site from appropriate clinic lists.

At each participating site, the control group will be recruited before recruitment to the intervention condition begins. Staff will be trained in the use of the intervention once control group recruitment has been completed at their site.

Women identified as being eligible for the control (usual care) group will be given the study information sheet together with a consent form and questionnaire booklet and a stamped – return addressed envelope. Clinic staff will provide these materials and be on hand to address any questions from potential participants (and will contact the research team for assistance if there are any questions they are unable to answer).

Women identified as being eligible for the intervention group will be given the study information sheet, and the opportunity to ask questions about the study. Those interested in taking part will be given a consent form and an appointment at which they will complete the PEGASUS intervention - this appointment will be not less than 24 h after they have first been told about the study (exact details will depend on the specific study site).

During the intervention consultation, women who have chosen to take part in this study will have a discussion with the trained PEGASUS coach that will be aimed at clarifying their explicit goals and expectations about reconstructive surgery. Together, the coach and patient will complete the PEGASUS sheet – a single piece of paper which will summarise the conversation and list explicitly what the patient is hoping breast reconstruction will achieve. The participant will then take this PEGASUS sheet into their consultation with the breast reconstruction surgeon, who will have been trained to use the sheet, to encourage a discussion about the woman’s expectations, thereby framing the surgical discussion in terms of what it is that the patient is hoping to achieve.

We will seek consent from women in the intervention condition to record their PEGASUS consultations in order that we can assess the fidelity of the intervention.

We will ask all participants to complete the following self-report measures in the questionnaire booklet at baseline (i.e. pre-intervention for those in the PEGASUS condition, equivalent timing for those in the control condition) and 3, 6 and 12 months after surgery, together with visual analogue scales (VAS) to assess the extent to which expectations/goals have been met, and satisfaction with decision making and care. Measures will be available for completion in paper format and online. Statistical analysis will examine changes in the self-report scores over time.

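### Training at each site is triggered by the close of control recruitment, not by the last control's surgical consultation, so late controls can be seen by PEGASUS-trained surgeons

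*Protocol article*

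**What the plan says.** The trigger for training appears twice in the Method. Procedure: "Staff will be trained in the use of the intervention once control group recruitment has been completed at their site". Design: "On completion of the control group recruitment, the health professionals receive PEGASUS training, prior to intervention group recruitment". Both name the close of recruitment as the event that releases training.

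The Intervention training section makes clear that this is not confined to the coaches: "Specialist nurses, psychologists and surgeons at each site will be trained to use PEGASUS".

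Baseline is defined in Procedure as "pre-intervention for those in the PEGASUS condition, equivalent timing for those in the control condition". The intervention itself has two steps, the coach session and then the surgical consultation: "The participant will then take this PEGASUS sheet into their consultation with the breast reconstruction surgeon, who will have been trained to use the sheet".

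The Design section explains the absence of randomisation partly by contamination: "contamination effects between conditions are likely if surgeons must focus some consultations around the patient goals offered by PEGASUS", with the same surgeons having to return to usual care for other patients.

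The Abstract (Methods) is looser. It describes control data collection out to 12 months after surgery and continues: "Health professionals will then be trained to use PEGASUS".

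**The concern.** A control is enrolled at a moment matched to the pre-intervention point, so her decision-making consultation with the surgeon can come after her recruitment. The rule asks only that recruitment be finished before training begins. At each site, the women recruited last may still be waiting for that consultation when their surgeon is trained. The Method states no requirement that control consultations be complete, and no interval between the close of recruitment and training.

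This needs no departure from the protocol; it can happen with full adherence. A surgeon newly trained to structure consultations around patient goals would have to set that aside for the remaining controls, which is the kind of switching that the Design section says makes contamination likely. Any carry-over moves the usual-care mean towards the PEGASUS mean. The expected bias is towards no difference, with a loss of power.

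**Working it through.** **Inputs from the document.** 90 women per group (Abstract, Power calculations); Cohen's d = 0.5, two-sided alpha 0.05, independent-samples t-test, stated power at least 90% (Power calculations); five named sites (Sites).

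**Inputs assumed, because the document gives neither.** m = number of controls whose consultation falls after training at their site; k = share of the PEGASUS effect that such a control receives. The standard deviation is held at 1.

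**Step 1: reproduce the plan's figure.** With d = 0.5 and n = 90 per group, the exact (noncentral t) power is 91.6%. The statement of at least 90% reproduces, with a margin of 91.6 − 90 = 1.6 points.

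**Step 2: dilute the effect.** If m of the 90 controls each receive a share k of the effect, the expected difference becomes

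d′ = 0.5 × (1 − (m/90) × k).

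For example, m = 10 and k = 0.5 gives d′ = 0.5 × (1 − 0.111 × 0.5) = 0.472.

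**Step 3: power at d′, 90 per group, exact t.** With five sites, m = 5, 10 and 20 correspond to one, two and four women per site.

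| m of 90 | k = 0.25 | k = 0.5 | k = 1 (upper bound) |
|---|---|---|---|
| 0 | 91.6% | 91.6% | 91.6% |
| 5 (5.6%) | d′ 0.493, 90.8% | d′ 0.486, 90.0% | d′ 0.472, 88.3% |
| 10 (11.1%) | d′ 0.486, 90.0% | d′ 0.472, 88.3% | d′ 0.444, 84.3% |
| 20 (22.2%) | d′ 0.472, 88.3% | d′ 0.444, 84.3% | d′ 0.389, 73.7% |

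**Step 4: read the bias from the same table.** The relative shrinkage of the difference is (m/90) × k. At k = 0.5 this is 2.8% for m = 5, 5.6% for m = 10 and 11.1% for m = 20.

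**Step 5: effect of the fix.** If no control is seen after training, m = 0, d stays at 0.5 and power stays at 91.6%. No extra participants are needed.

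**Step 6: does the Abstract close the gap?** Read as a strict sequence, it would put training after control follow-up, and m would be 0. But it sets no rule, and it does not match the specific trigger given in both Design and Procedure. The three places need to be reconciled.

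**The case against.** The strongest reply is that this is a small tail, not a failure of the design. Most controls would still be seen by untrained surgeons. The contamination described in Design is continuous alternation between two ways of consulting throughout a randomised trial, which is a far larger exposure than a few women around a training date. That stands, and it is why the point is put as a partial reopening of the risk.

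A reader might infer that the rule defeats the design's whole purpose, because contamination was the only ground for not randomising. The document does not support this. Design first says, more generally, that randomised trials do not always suit psychosocial research. Contamination is the study-specific reason, not the sole one.

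A reader might also infer that the difference will be diluted, or that the stated 90% is bound to be lost. Neither follows. The document gives no interval from enrolment to consultation, or from the close of recruitment to training, so m may be zero at some sites. One woman per site at half the effect leaves power at about 90.0%; two per site at a quarter of the effect does the same. Because the margin is only 1.6 points, crossing 90% is in any case a weak test of harm. Full transfer is implausible on the document's own description, since a late control has neither the coach session nor the sheet.

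It is also fair to say that the timing is inferred: "equivalent timing for those in the control condition" does not state outright that controls enrol before their consultation, although a match to the pre-intervention point is hard to read otherwise. Controls return their booklet by post, which may shorten the gap between enrolment and consultation.

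Lastly, an article condenses a fuller protocol, and site scheduling may be set out there. That would excuse silence. It does not excuse an explicit trigger, given twice and tied to the wrong event.

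**Conclusion.** The concern holds in a limited form. The stated rule allows late controls to be seen by PEGASUS-trained surgeons, and this can dilute the comparison towards no effect. The size is unknown. Under the assumption that 5 to 20 of the 90 controls are affected and receive half the effect, power falls from 91.6% to between about 90% and 84%, and the estimated difference shrinks by about 3% to 11%. The full-transfer column, down to 73.7%, is an unlikely upper bound and should not be quoted as the expected loss. These figures rest on assumed m and k, a constant standard deviation and the plan's own d = 0.5. The change is worth making because it is cheap and protects the contrast that the sequential design was chosen to preserve.

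**What to change.** 1. In Design and Procedure, tie training at a site to the date on which the last control recruited there has had the surgical consultation at which her reconstruction decision is made. Bring the Abstract's account of the sequence into line.
2. Record the date of that consultation for every control, and the training date for every site.
3. Add a sensitivity analysis that excludes controls whose consultation fell after training at their site, and report how many there were. This also covers sites where training has already taken place.

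The cost is a change of wording, two recorded dates and a delay at each site before training. The document gives no basis for saying how long that delay would be. It also lengthens the calendar gap between the groups, which in a non-randomised before-and-after comparison modestly increases exposure to secular trend, a bias that could go in either direction. If the delay at a site would be long, the dates and the sensitivity analysis still allow the effect of late controls to be examined.
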